### Data Analyses

#### Effect Analyses

All analyses will be performed in SPSS (IBM Corp). Baseline characteristics will be summarized using descriptive statistics and compared between the intervention and control group using *t* tests, Mann-Whitney U tests, chi-square tests, or Fisher exact tests. Survival analysis will be used to analyze time until RNA data. Both crude and adjusted analyses will be performed. Hospital, surgical procedure, and sex will be taken into account as covariates in the adjusted analyses because these are the factors for which stratification will apply. In addition, when there are clinically relevant differences between the intervention and the control group in the baseline characteristics or potential confounding factors, this will also be considered as a covariate in further analyses. To describe the distribution of the duration until RNA in both groups, the Kaplan-Meier method will be used. The Cox proportional hazard model will be applied to calculate HRs. Differences in secondary outcomes between the groups will be assessed by mixed models and multilevel logistic regression models for outcomes that are measured more than once during follow-up, and *t* tests, Mann-Whitney U tests, chi-square tests, or Fisher exact tests will be used when differences on 1 time point will be compared. Statistical analyses will be performed according to intention-to-treat principle, which will be compared to per-protocol analyses. Patients will be included in the per-protocol analyses when they used the intervention as intended, which will be defined as the generation of a convalescence plan on the website. This will be measured by a web log. Subgroup analyses will be performed regarding the surgical procedure (1. Cholecystectomy, 2. Hernia inguinal surgery and 3. Adnexal surgery) and type of surgery (gynecological vs surgical procedures). A post hoc analysis will be carried out on patients without major complications (definition described in Potential Confounding Factors).

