###### Postoperative Consult by eConsultation Instead of Consultation in the Outpatient Clinic

At discharge, patients from the intervention group will not receive a standard appointment at the outpatient clinic. Instead, they are offered continuous guidance via the website (information, feedback on recovery) and the possibility to ask questions on the website to a health care professional from their own hospital by means of an eConsult in case of recovery problems (Figure 6). They are informed that the question will be answered within 2 working days except for urgent matters. In that case, they receive a phone number for direct contact. In addition patients will receive a telephone call 2 weeks after surgery to inform them about any test results. Various studies already have proven that telephone follow-up is feasible and effective after the type of surgical procedures which are included in this study [26-28]. The telehealth follow-up aims to replace the standard single postoperative consultation in the outpatient clinic to increase access to care, reduce patient uncertainties and fear related to the recovery process, reduce costs and workload, and meet patient preferences of care during out-of-office hours [29,30]. We hypothesize that patients will be more comfortable and less hampered in resuming their activities with the opportunity to ask questions whenever they prefer instead of the standard consultation several weeks after surgery.

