#### Potential Confounding Factors

Major complications during surgery (eg, conversion to an open procedure), major complications in the postoperative course (eg, leading to a prolonged hospital stay of more than 2 nights after surgery), and readmission to the hospital in the 30 days after surgery or repeated surgery in the 30 days after surgery are considered as potential confounders. The complications will be assessed by reviewing the surgical reports and postoperative notes.

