### Sample Size Calculation

Previous studies evaluating this type of intervention on RNA are lacking. We based our sample size calculation on the outcomes on RTW after gynecological surgery of our previous study [16]. Based on this study we expected a hazard ratio (HR) of 1.4 for RNA using the optimized intervention. Considering an HR of 1.4 and using a 2-sided log-rank test at a significance level of 5%, we need to observe 285 events (patients returning to normal activities) to achieve a power of 80%. The total sample size is set at 308 (154 per arm) to account for an anticipated proportion of 2.5% of patients not returning to daily activities within the 6-month follow-up period and a dropout rate of 5%.

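### Events that occur after randomisation (complications, prolonged stay, readmission, reoperation) are candidate covariates when the arms differ, so the adjusted hazard ratio may not estimate the intention-to-treat effect

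*Protocol article*

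**What the plan says.** Under Allocation, the protocol article randomises patients once the T0 questionnaire is complete, in the month before surgery.

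The section Potential Confounding Factors lists major intraoperative complications (such as conversion to open surgery) and major postoperative complications (such as a stay of more than 2 nights). It adds that "readmission to the hospital in the 30 days after surgery or repeated surgery in the 30 days after surgery are considered as potential confounders".

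Effect Analyses plans crude and adjusted survival analyses. Hospital, procedure and sex are the fixed covariates. Others are to be considered "when there are clinically relevant differences between the intervention and the control group in the baseline characteristics or potential confounding factors". The same section adds: "A post hoc analysis will be carried out on patients without major complications". It does not say whether the crude or the adjusted hazard ratio is the primary result.

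The intervention changes care before and after surgery. It gives tailored advice on resuming activities and on when to seek help, sends alerts when recovery is delayed, and offers eConsult and a telephone call at 2 weeks. At discharge, "patients from the intervention group will not receive a standard appointment at the outpatient clinic". Under Blinding, health care providers are not blinded.

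**The concern.** A confounder of a randomised comparison would have to precede allocation. Every factor in the list follows it. An imbalance in such a factor is either chance or an effect of the allocated programme, and the data cannot tell the two apart.

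The trigger makes this worse. A between-arm difference is what prompts adjustment, and a difference is also what one would see if the programme changed these events. Adjustment then removes whatever part of the effect runs through them. The analysis restricted to patients without complications conditions on the same events.

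The trial asks whether eHealth can partly substitute usual postoperative care. Any effect on complications, readmission or reoperation, in either direction, belongs in that answer.

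**Working it through.** **1. Order of events**

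| Factor (Potential Confounding Factors) | Timing against randomisation | Plausible route from the programme |
|---|---|---|
| Major intraoperative complication | After | None evident |
| Major postoperative complication, stay over 2 nights | After | Weak for the index stay: mainly preoperative preparation and unblinded providers. Resumption advice, alerts and eConsult matter mostly after discharge |
| Readmission or reoperation within 30 days | After | Advice, alerts, eConsult, 2-week call, unblinded providers |

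None precedes randomisation, so none is a baseline covariate.

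**2. The plan's own figures**

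Inputs from Sample Size Calculation: HR 1.4, two-sided 5%, power 80%, 2.5% without the event, 5% dropout.

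- Schoenfeld: 4 × (1.960 + 0.842)² / (ln 1.4)² = 4 × 7.849 / 0.1132 = 277.3, so 278 events.
- Freedman: 7.849 × (2.4 / 0.4)² = 282.6, so 283 events.
- Power with 285 events: Φ(√285 / 2 × 0.3365 − 1.960) = Φ(0.880) = 0.81.
- Patients: 285 / (0.975 × 0.95) = 307.7, so 308.

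The stated 285 and 308 hold up and do not depend on the covariate rule.

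**3. Illustration (every input assumed)**

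Time to return to normal activities is exponential, with a median of 30 days in uncomplicated controls and censoring at 182 days. A complication multiplies the hazard by 0.3. Cox models were fitted to 6 simulated data sets of 20,000 patients per scenario.

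| Direct HR | Complications, control / intervention | Crude HR (total effect) | Adjusted for complication | Complicated patients excluded |
|---|---|---|---|---|
| 1.4 | 5% / 5% | 1.37 | 1.41 | 1.41 |
| 1.4 | 5% / 10% | 1.26 | 1.41 | 1.41 |
| 1.4 | 5% / 15% | 1.17 | 1.41 | 1.42 |
| 1.0 | 5% / 10% | 0.93 | 1.01 | 1.01 |

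The simulation standard error of a log HR is about 2 / √120,000 = 0.006, so 1.01 and 1.41 are compatible with the direct effects of 1.00 and 1.40.

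The crude column can be checked without simulation. With λ = ln 2 / 30, direct hazard ratio h (1 in control) and complication probability p, each arm has S(t) = (1 − p) exp(−λht) + p exp(−0.3λht) and density f = −dS/dt. The crude log HR β solves ∫ {f₁ − (f₀ + f₁) e^β S₁ / (S₀ + e^β S₁)} dt = 0 over 0 to 182 days. The four rows give 1.36, 1.25, 1.16 and 0.93. With 7% against 10% and no direct effect, the result is 0.96.

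In the first row the programme does not affect complications. Its gap of 1.37 to 1.41 is mostly non-collapsibility of the hazard ratio. The part carried by complications is the fall in the crude column, from 1.37 to 1.26 and 1.17.

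**4. Scale**

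ln 0.93 = −0.073, which is 0.073 / 0.336 = 22% of the design log HR. With 285 events the standard error is 2 / √285 = 0.118, so moving from 0.93 to 1.00 is about 0.6 standard errors. An observed HR of 0.93 would have a 95% confidence interval of exp(−0.073 ± 1.96 × 0.118), that is 0.74 to 1.17.

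**The case against.** Several points for the plan stand.

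- The crude analysis is retained, so the total effect will be estimated, and the fixed covariates are only the stratification factors.
- The wording is that such a factor is considered as a covariate, not that it is always entered.
- The complication-free analysis is already labelled post hoc.
- Adjusting for an intraoperative event that the programme cannot influence does little harm.
- The shift in the illustration is smaller than one standard error, and no rate in it comes from the documents.

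Stronger readings are tempting but not supported.

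- A reader might infer that dropping the outpatient visit causes these events. Control Group places that visit at 4 to 8 weeks, so from about day 28. It barely overlaps the 30-day window and cannot explain intraoperative events or a long index stay. Any plausible route is the programme as a whole.
- A reader might infer that an excess of readmissions would go unreported. The crude HR keeps its effect, the covariate rule itself requires the arms to be compared on these events, and hospital care enters the cost analysis.
- Collider bias is possible in principle, but the illustration has no common cause of complications and recovery that acts on both, so it does not show it.

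These points limit the concern without removing it. Without a named primary model, the choice between a crude and a complication-adjusted HR stays open until the arms have been compared on the very events in question. Labelling an analysis post hoc does not restore the randomised comparison. Nor is this a detail left to an analysis plan: the article states the rule, and the rule is wrong.

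**Conclusion.** The covariate rule is wrong as written, because it treats events after randomisation as confounders. The resulting bias is conditional. It needs the programme to affect postoperative complications, readmission or reoperation, and it needs the covariate to be entered. The documents establish neither, so it would go too far to say that the estimate is biased.

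If both hold, the adjusted HR no longer estimates the total intention-to-treat effect. Under the assumed 5% against 10% with multiplier 0.3 and no direct effect, about 0.93 becomes about 1.00. With 7% against 10%, about 0.96 becomes about 1.00. Reversing the rates would hide a benefit in the same way. These figures show direction and order of size only.

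**What to change.** 1. In Effect Analyses, strike the reference to potential confounding factors from the covariate rule, leaving baseline characteristics only.
2. Name as primary the Cox model adjusted for hospital, procedure and sex, plus any baseline covariates fixed in advance.
3. Compare major complications, stay over 2 nights, 30-day readmission and 30-day reoperation between arms by intention to treat, for example as risk differences with 95% confidence intervals.
4. Describe any complication-adjusted or complication-free analysis as exploratory and not as an estimate of the randomised effect.

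The cost is a change of wording and one table. The events are already to be collected from surgical reports and postoperative notes. The 285 events and 308 patients stay as they are. The article reports that analysis had not begun at submission, so at that point the change could still be made before any results were seen.

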	**Secondary outcome measures**									
		Participation (PROMIS short form Social Roles)		X		X	X	X		X
		Self-rated health (EuroQol-5D-3L)		X			X	X	X	X
		Return to work (Return to work questionnaire)				X	X	X	X	X
		Physical activity (IPAQ^c^)		X			X	X	X	
		Recovery (RI-5^d^)		X		X	X	X		
		Pain intensity (VAS^e^)				X	X	X		
		Patient satisfaction (Satisfaction questionnaire)							X	

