#### Prognostic Factors

Before surgery (T_0_), various sociodemographic data will be assessed (sex, age, level of education, living conditions, working conditions) and questions asked regarding expectations about the length of recovery. Also the T-scores of the PROMIS physical functioning short forms conducted by the patient will be calculated.

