### Allocation

After inclusion, patients will be asked to complete the first online questionnaire (T_0_) within the month before surgery. After patients have completed the questionnaire, randomization will take place by means of a computer-based randomization list stratified regarding hospital, sex, and surgical procedure using permuted blocks, size 2. Patients are randomized to the intervention or the control group in a 1:1 ratio. The researcher performing randomization is independent from the recruitment or data analyses.

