### Data Collection

Data will be collected by means of self-reported electronic questionnaires at standard moments. Data will be collected in the month before surgery (T_0_) and 1 week (T_1_), 3 weeks (T_2_), 6 weeks (T_3_), 3 months (T_4_) and 6 months (T_5_) after surgery (Table 2). When data regarding RNA are missing during 2 measuring moments, an attempt will be made to collect the missing questions by telephone or email.

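### For five repeated secondary scales, the stated covariate rule gives the outcome's own pre-randomisation T0 value no unconditional place, which can give up precision when the arms look balanced

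*Protocol article*

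**What the plan says.** **Model.** The protocol article, Effect Analyses, says: "Differences in secondary outcomes between the groups will be assessed by mixed models and multilevel logistic regression models for outcomes that are measured more than" … The rest of the sentence confines this to outcomes with repeated follow-up measurements. Comparisons at a single time point use simple two-group tests.

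**Covariates.** Earlier in the same paragraph, after survival analysis is named for the primary outcome, comes: "Hospital, surgical procedure, and sex will be taken into account as covariates in the adjusted analyses because these are the factors for which stratification will" … Anything else is considered as a covariate in further analyses only "when there are clinically relevant differences between the intervention and the control group in the baseline characteristics or potential confounding factors" are found.

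**T0 data.** Data Collection sets the schedule: "Data will be collected in the month before surgery (T_0_) and 1 week (T_1_), 3 weeks (T_2_), 6 weeks (T_3_), 3 months (T_4" … The last time point, T5, is at 6 months. Table 2 marks T0 for these repeated secondary scales:
- PROMIS physical function (the item-bank row), followed at T1 to T5.
- Social participation, the row "Participation (PROMIS short form Social Roles", followed at T1, T2, T3 and T5.
- EQ-5D-3L, the row "Self-rated health (EuroQol-5D-3L", followed at T2 to T5.
- IPAQ, followed at T2, T3 and T4.
- RI-5, followed at T1, T2 and T3.

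The Prognostic Factors section, on the period before surgery, adds: "Also the T-scores of the PROMIS physical functioning short forms conducted by the patient will be calculated".

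**Order.** Allocation says: "After patients have completed the questionnaire, randomization will take place". T0 therefore precedes allocation and should be close to complete in randomised patients.

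**The concern.** A baseline measurement of the outcome sharpens a treatment comparison in proportion to how well it predicts the follow-up values. That holds whether or not the arms happen to differ at baseline. A rule that admits baseline variables only when a difference is seen uses a criterion unrelated to this gain. Randomisation usually produces arms that look alike, and in that case the rule leaves a prognostic T0 score out. The choice of model also comes to depend on the data, through a threshold for clinical relevance that the article does not define.

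The article itself lists the T0 physical function score among prognostic factors, yet gives it no fixed role in the analysis. At stake is the width of the confidence intervals for the five scales that describe function, participation, health status, activity and recovery beyond the primary endpoint.

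**Working it through.** **1. The plan's own figure.** The only sample size calculation is for the primary outcome: hazard ratio 1.4, two-sided 5%, 80% power, 285 events, 308 patients.
- Freedman: (1.960 + 0.842)² × (2.4/0.4)² = 282.6, so 283 events.
- Schoenfeld: 4 × (1.960 + 0.842)² / (ln 1.4)² = 277.3, so 278 events.
- Patients: 285 / (0.975 × 0.95) = 307.7, so 308.

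The stated figures reproduce to within 3%. No power is stated for any secondary outcome.

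**2. Inputs for the illustration.** Patients per arm: 154 × 0.95 = 146, using the plan's 5% dropout. The correlation between T0 and follow-up (ρ) is not in the documents. It is **assumed** and shown as a range. Because hospital, procedure and sex would already be in the model, ρ should be read as the correlation that remains after them.

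**3. One follow-up time point.** The standardised difference detectable with 80% power without T0 is 2.80 × √(2/146) = 0.33. Adjusting for T0 multiplies the variance by 1 − ρ², so power becomes Φ(2.80/√(1 − ρ²) − 1.96).

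| ρ | Variance ratio | Power with T0 |
|---|---|---|
| 0.1 | 0.99 | 80.4% |
| 0.2 | 0.96 | 81.6% |
| 0.3 | 0.91 | 83.6% |
| 0.4 | 0.84 | 86.4% |
| 0.5 | 0.75 | 89.9% |

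**4. Average over m follow-ups.** Let ρ be the T0-to-follow-up correlation and f the correlation between follow-ups. The variance is proportional to V₀ = [1 + (m − 1)f]/m without T0, and to V₀ − ρ² with it. The starting point is again 80% power without T0. Example with m = 4, ρ = 0.3, f = 0.5: V₀ = 2.5/4 = 0.625; with T0 it is 0.625 − 0.09 = 0.535; the ratio is 0.856.

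| ρ | f | Ratio, m = 3 / 4 / 5 | Power, m = 3 / 4 / 5 |
|---|---|---|---|
| 0.2 | 0.5 | 0.940 / 0.936 / 0.933 | 82.4 / 82.5 / 82.6% |
| 0.3 | 0.5 | 0.865 / 0.856 / 0.850 | 85.4 / 85.7 / 86.0% |
| 0.5 | 0.7 | 0.688 / 0.677 / 0.671 | 92.2 / 92.6 / 92.8% |
| 0.5 | 0.5 | 0.625 / 0.600 / 0.583 | 94.3 / 95.1 / 95.6% |

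IPAQ and RI-5 have three follow-ups, social roles and EQ-5D-3L four, and physical function five.

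**5. Reading the results.** At ρ of 0.1 to 0.2 the gain is negligible to small. At 0.3 it is under 5 points at one time point and about 5 to 6 points for the average with f = 0.5. At 0.5 it is about 10 points at one time point and 12 to 16 for the average. These formulas are for quantitative outcomes. They do not carry over directly to a scale that is dichotomised and analysed by logistic regression.

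**The case against.** **The article never says that T0 is left out.** It names a model family and gives no fixed effects. Limiting mixed models to outcomes with repeated follow-up decides which outcomes get that method, not which terms go in. T0 could enter as a covariate or as a first repeated measure, and a full protocol or analysis plan that is not shown may settle this. All of that stands. A reader might infer that the trial has decided to analyse these scales without T0, and the text does not support that. The point rests on what the article does state, namely a conditional rule for baseline variables, and not on its silence about the mixed models.

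**The rule may not reach the secondary models.** The covariate sentences sit between the survival analysis and the Kaplan-Meier and Cox sentences. That they extend further is inferred from the reference to further analyses. This also stands. If they do not extend, the article fixes no covariates for these models, and the proposed sentence would still settle the matter.

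**The gain may be small.** Surgery lies between T0 and every follow-up, so the correlation may be modest, especially at 1 and 3 weeks. Procedure and sex may already explain part of the T0 spread. Both are fair, which is why the range starts at 0.1. The documents say nothing about how widely T0 scores vary between patients, so no claim is made on that.

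**Not every secondary outcome is affected.** A reader might infer that all secondary intervals are wider than they need be. Table 2 shows no T0 value for return to work, pain or satisfaction, and the times to first activity and to 75% of activities are time-to-event outcomes. None of these is touched.

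**Conclusion.** The point holds as a modest, nearly free improvement. For five scales with a pre-randomisation measurement, the article's only stated route for T0 into the model is an observed difference between the arms, and that criterion does not track the precision at stake. The size cannot be fixed from the documents. Under the assumed correlations of 0.1 to 0.5, power at one time point rises from 80% to between about 80% and 90%. The gain is somewhat larger for the average over follow-ups, and smaller where the stratification factors already account for part of the T0 spread.

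The conclusion rests on two readings: that the covariate rule carries over to the secondary models, and that no document outside this article already prescribes T0 adjustment. It concerns precision only. There is no bias, and the primary Cox model, the 285 events and the 308 patients are unaffected.

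**What to change.** Add one sentence to Effect Analyses: for the PROMIS physical function T-score, PROMIS social roles, EQ-5D-3L, IPAQ and RI-5, the mixed model includes the outcome's own T0 value as a covariate in all cases, together with hospital, surgical procedure and sex, whether or not the arms differ at baseline. Make this the main analysis for those outcomes. Outcomes without a T0 value keep the stratification factors only.

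The cost is one extra model term per outcome. It needs no new data, and because T0 is completed before randomisation, essentially no patients are lost. The Results section says that analyses had not begun at submission, so the term could still be specified in advance.

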#### Primary Outcome

The primary outcome measure of the study will be time to return to normal activities (RNA). The Patient-Reported Outcomes Measurement Information System (PROMIS) Physical Functioning item bank version 1.2 will be used to measure limitations in daily activities. This item response theory (IRT)–based item bank has been developed and validated in the United States and translated into Dutch-Flemish [31,32]. Initial validation studies in Dutch patients confirmed the unidimensionality and underlying calibration of the IRT model (personal communication, article submitted). This item bank consists of 121 activities. We made a selection of the 29 most relevant activities for this study (Multimedia Appendix 2). We considered the 92 excluded activities as not being affected by the type of surgery (eg, “Can you brush your hair?”) or as duplicate activities. The list of 29 activities will be presented to the patients at baseline (prior to surgery), and they will be asked to select 8 activities which are most relevant for them in daily life. In this way, patients will design their own personal physical functioning short form. Since items in an IRT-based item bank are calibrated onto the same continuum, one can select any subset of questions in that bank and the scores obtained from the derived short forms are comparable to that from the complete bank [33]. In the follow-up questionnaires, patients will only receive those PROMIS questions regarding the 8 activities that they selected before surgery as relevant to their personal life. Items are scored on a 5-point scale with 1 as most limited and 5 as no limitation. In addition, they will be asked postoperatively whether they can perform this activity on the same level as before surgery. If they answer “yes,” they are asked to fill in since when (date), and the question will no longer be repeated in the following questionnaires. If the question is answered with a “no,” the question will be asked again at the next follow-up moment. For each patient, this will result in 8 dates of resumption of their activities. These dates will be converted into time periods by calculating the number of days that have elapsed between the date of surgery and the date of the resumption of that particular activity. The moment of resumption of the last activity on the list will be defined as the RNA moment and thus the primary outcome measure will be time elapsed between surgery and resumption of the last activity. If patients have not resumed 1 or more activities at 6 months, those activities will be censored. If information about the resumption of 2 or fewer activities is missing, the RNA moment will be calculated based on 6 activities. If information about the resumption of more than 2 activities is missing, the RNA moment cannot be calculated accurately and will be considered as missing data.

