
#### Secondary Outcomes

As secondary outcomes we will use the time until the first activity can be resumed and the moment that 75% of the activities are resumed. Scores of the physical functioning short forms will also be calculated by summarizing for each patient the scores of the 8 activities and transforming them into a T-score on the PROMIS physical functioning metric, where 50 represents the average score of the US population with an SD of 10. The following outcomes will also be measured:

Social participation: assessed with the PROMIS Ability to Participate in Social Roles and Activities version 2.0 short form 8a [34]Self-rated health: measured by the 3-level EuroQol-5D (EQ-5D-3L) [35]Durations of return to work (RTW) (only for the working population): the time until the first day on which work will be resumed and the time until full resumption of work activities will be assessedPhysical activity: assessed by the International Physical Activity Questionnaire (IPAQ) short form [36]Length of recovery: measured by the recovery specific quality of life questionnaire (RI-5) short form [37].Pain intensity: measured by the Von Korff questionnaire visual analog scale (VAS) [38].Patient satisfaction: measured with a self-developed patient satisfaction questionnaire focused on satisfaction with perioperative care, the care program (both groups), the website (both groups), the app (intervention group only), and the activity tracker (intervention group only).

**Table 2 table2:** Outcome measures, measurement instruments, and time points.

				Enrollment	Surgery	Post-allocation				
Time Point^a^				*T* _0_		*T* _1_	*T* _2_	*T* _3_	*T* _4_	*T* _5_

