#### Economic Evaluation

The economic evaluation will be performed from a societal and health care perspective. The time horizon of the economic evaluation is 6 months, thus discounting of costs and effects is not necessary. Both cost-effectiveness and cost-utility analyses will be performed. The cost-effectiveness analysis will be performed with the primary effect measure (ie, RNA). The cost-utility analysis will be performed with quality-adjusted life-years (QALYs). The patients’ EQ-5D-3L health states will be converted into utilities using the Dutch tariff, and QALYs will be calculated using linear interpolation between measurement points [43]. The analyses will be done according to the intention-to-treat principle. Missing cost and effect data will be imputed using multiple imputation after which results will be pooled using Rubin’s rules [44]. Cost and effect differences will be analyzed using multilevel analyses with a 2-level structure (ie, patient, hospital). The 95% CIs around the cost differences will be estimated using bias-corrected intervals with 5000 replications. The bootstrap replications will be stratified for hospital to account for the clustering of data [45]. Incremental cost-effectiveness ratios (ICERs) will be calculated by dividing the difference in mean total costs between the groups by the difference in mean effects. Uncertainty surrounding the ICERs will be graphically presented on cost-effectiveness planes. Cost-effectiveness acceptability curves will also be estimated illustrating the probability that the optimization and substitution of perioperative care by eHealth is cost effective in comparison with usual care for a range of different ceiling ratios. Various sensitivity analyses will be performed to assess the robustness of the results.

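### Four secondary outcomes are times to an event, but the analysis rule sends all secondary outcomes to methods that cannot use times cut short by dropout

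*Protocol article*

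**What the plan says.** **Outcomes.** The Secondary Outcomes section names two durations built from the eight activity dates: "the time until the first activity can be resumed and the moment that 75% of the activities are resumed". For working patients it adds two more: "the time until the first day on which work will be resumed and the time until full resumption of work activities".

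**Censoring.** The Primary Outcome section states: "If patients have not resumed 1 or more activities at 6 months, those activities will be censored". It handles missing activity dates by a separate rule, so censored and missing are different things in this plan.

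**Methods.** Effect Analyses says: "Survival analysis will be used to analyze time until RNA data". Kaplan-Meier and Cox are named in that context. For the rest it says: "Differences in secondary outcomes between the groups will be assessed by mixed models and multilevel logistic regression models", for outcomes measured more than once during follow-up. For the other case it lists t tests, Mann-Whitney and chi-square tests, and "Fisher exact tests will be used when differences on 1 time point will be compared". Durations are given no exception.

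**Economic evaluation.** RNA is the effect measure, the time horizon is 6 months, and the ratio is formed by "dividing the difference in mean total costs between the groups by the difference in mean effects". Multiple imputation is planned for missing cost and effect data. How a censored RNA time enters the mean is not stated.

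**The concern.** A patient who has not returned to work when follow-up ends, or who stops answering at week 6, has a duration known only to exceed some value. Kaplan-Meier and Cox use that information. A t test, a Mann-Whitney test or a mixed model of the duration does not. An analyst following the rule must either drop such patients or enter the cut-off as if it were an observed time.

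Dropping them conditions on having returned. If the programme works, the control arm has more late returners, so deletion removes more long times from that arm and shrinks the estimated benefit.

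The rule also splits data of one kind. RNA is the last of the eight activity dates, and the 75% outcome is the sixth (0.75 × 8 = 6). Both come from the same questionnaires with the same 6-month limit, yet the last date goes to Cox and the sixth does not.

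**Working it through.** **1. The plan's own figures.** Inputs from Sample Size Calculation: hazard ratio 1.4, two-sided 5%, power 80%, 285 events, 2.5% not returned by 6 months, 5% dropout, N = 308.
- Schoenfeld: (1.960 + 0.842)² × 4 / (ln 1.4)² = 277.3, so 278 events.
- Freedman: (1.960 + 0.842)² × (2.4/0.4)² = 282.6, so 283 events.
- Both lie within 3% of the stated 285. N = 285 / (0.975 × 0.95) = 307.7, so 308.

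The design reproduces, and nothing here changes it. The same inputs imply about 8 patients not returned at 6 months (0.025 × 308 = 7.7) and about 15 dropouts (0.05 × 308 = 15.4).

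**2. Which durations are exposed.**
- *Time to 75% of activities:* never later than RNA in the same patient, so non-return should not exceed the 2.5% expected for RNA. Dropout applies as well.
- *Time to first activity:* rarely censored.
- *First and full return to work:* the article states no censoring rule. Censoring follows from the 6-month follow-up and the 5% dropout. No return-to-work distribution is given.

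**3. Effect of deleting non-returners (illustration).** Assumptions: exponential times, hazard ratio 1.4, follow-up to 183 days. With rate λ = ln 2 / median (times 1.4 in the intervention arm):
- not returned: S = exp(−183λ)
- mean restricted to 183 days: R = (1 − S)/λ
- mean among those returned: C = (R − 183·S)/(1 − S)

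Control median 40 days: λ = 0.01733 and 0.02426; S = 4.2% and 1.2%; R = 55.29 and 40.73; C = 49.69 and 39.03.

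| Control median (days) | Difference in R (days) | Difference in C (days) | Shrinkage |
|---|---|---|---|
| 40 | 14.6 | 10.7 | 27% |
| 30 | 11.8 | 10.2 | 14% |
| 20 | 8.2 | 7.9 | 3% |

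At 40 days the average not returned is (4.2 + 1.2)/2 = 2.7%, close to the plan's 2.5% for RNA.

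**4. Power (simulation, exponential times, hazard ratio 1.4, about 2.5% not returned).**
- 146 per arm (154 less 5%), no further dropout: log-rank 0.80. Mann-Whitney gives 0.705 with non-returners tied at 183 days and 0.705 with no censoring at all.
- 154 per arm, with 5% dropping out at random times: log-rank 0.83; Mann-Whitney with censored times treated as observed 0.71; Mann-Whitney after deletion 0.58; t test after deletion 0.65.

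The gap between 0.80 and 0.705 is therefore the lower efficiency of the rank test under proportional hazards, not a censoring effect. The further fall to 0.58 comes from deletion. Return to work concerns working patients only, so absolute power there would be lower under every method.

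**The case against.** **Nothing says that non-returners are deleted.** This is correct. The article censors unresumed activities, keeps censored apart from missing, and specifies intention-to-treat. The shrinkage figures are conditional on a step that the rule leaves open but does not prescribe.

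**A rank test can cope with a common 6-month cut-off.** This also stands. Non-returners can be tied at the longest time, and the simulation shows no loss from doing so. The argument fails for the expected 5% dropout: a patient lost at week 6 cannot be placed last, nor treated as having returned at week 6.

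**The ICER needs a mean that censored data cannot identify.** A reader might infer this, but the article does not support it. It fixes a 6-month horizon, and the mean restricted to 6 months is identified. Only an unrestricted mean would not be, and the article never asks for one. What remains is that the restricted mean is implied rather than stated.

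**A large benefit could almost vanish.** One can build a case with this result. If the only effect is to cut slow returners from 15% to 5%, with assumed medians of 25 days for the others and 200 days for slow returners, a restricted-mean gain of 10.0 days appears as 2.5 after deletion. That case needs deletion and about 5.9% not returned, more than twice the 2.5% that the article expects for RNA. It does not indicate the likely size.

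**Return to work must yield a hazard ratio to compare with the earlier trial.** The planned 1.4 does rest on that trial's return-to-work outcome, but no formal comparison across trials is planned. A hazard ratio would be useful, not required.

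**The method could be left to the analysis plan.** This does not stand for the effect analyses. The article states a rule for all secondary outcomes, and the rule does not fit these four.

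**Conclusion.** The point holds at moderate severity. The stated rule gives durations with incomplete follow-up to methods that cannot use times censored by dropout. It matters mainly for both return-to-work durations and the time to 75% of activities. For time to first activity it is close to nil.

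If non-returners were deleted, the difference would shrink by roughly 3% to 27% for control medians of 20 to 40 days, assuming exponential times and a hazard ratio of 1.4. If they are kept and ranked last, the cost is mainly power, about 0.70 against 0.80 under proportional hazards. The medians are assumptions, because the article gives no distribution for these outcomes.

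A reader might go further and call this an error that must be corrected before the trial can be interpreted. The documents do not support that: RNA is correctly assigned to Kaplan-Meier and Cox, and the sample size and primary conclusion do not depend on the rule for secondary outcomes.

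**What to change.** In Effect Analyses, state that first and full return to work, time to first activity and time to 75% (6 of 8) of activities are analysed like RNA: Kaplan-Meier curves and a Cox model adjusted for hospital, sex and surgical procedure, with patients who have not returned censored at their last completed questionnaire. Keep mixed models and t or Mann-Whitney tests for the score outcomes.

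In Economic Evaluation, state that the effect is mean RNA time restricted to the 6-month horizon, with censored patients kept in.

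The cost is about two sentences. No new data are needed, and the article reports that data cleaning and analysis had not begun at submission.
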